#### Analysis

We will use descriptive analysis to compare baseline characteristics of emergency departments and individuals. For the primary analysis, an intent-to-treat hierarchical (mixed-effects) logistic regression model will be fit to compare the proportions of patients who experienced the primary outcome in the intervention and control arms. This model will adjust for baseline characteristics at both the emergency department (eg, prestudy emergency department revisit/hospitalization rate, service area population) and patient (eg, age, gender) level. As hospital records will supply emergency department revisit/hospital admission data, missed outcome events will be rare. Monitoring data will be analyzed using statistical process control charting techniques to allow a more comprehensive understanding of patient’s health condition over time.

#### Sex and Gender Analysis

No sex and/or gender specific analysis will be conducted. While there may be some sex differences in the incidence and prevalence of heart failure, our intervention is intended to establish a mechanism for the prevention and management of symptoms common to both groups. However, if sex and/or gender themes were to arise out of the qualitative data collected regarding patient experience, they would be explored.

#### Cost-Effectiveness Evaluation

Cost-effectiveness analysis and cost-utility analysis will be conducted. We will assess the incremental costs of the home monitoring platform relative to usual care and further track costs related to all utilization during the 90-day postdischarge period. Utilization will include hospital admissions, emergency department visits, community family physician and other health provider visits, drugs, and laboratory and other tests obtained outside the hospital. Utilization will be captured through hospital administrative databases and a simple resource utilization questionnaire administered to patients at the time of patient outcome data collection. The questionnaire will be developed during the study. In order to evaluate cost effectiveness, administrative data regarding health services utilization (in particular, emergency department revisits/hospitalizations) for cases and controls will be compared. Differences in utilization rates will then be used to determine differences in cost for both patient groups based on average costs for heart failure patients. Incremental costs will be compared to incremental benefits (ie, primary and secondary outcomes) in order to determine the cost per life year gained and cost per quality adjusted life year gained. A societal perspective will be taken in the analysis as both government and patient out-of-pocket costs will be captured. Probabilistic sensitivity analysis will be conducted in order to assess the robustness of the results through variation of key parameters.

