#### Process and Outcome Measurement

For both the feasibility study (Study 1) and cluster RCT (Study 2), the primary outcome goal is to reduce emergency department revisits/admissions measured by the proportion of patients who have an emergency department visit or admission within 90 days following discharge. This will be measured via hospital data and patient self-report postintervention. This aligns with the Triple Aim goal of improving population health [24]. Secondary outcomes related to the Triple Aim goal of cost effectiveness are reduction in cost as compared to usual care measured by utilization relative to patient outcomes and experience measured via hospital data as well as patient self-report. Reduction in cost metrics to ascertain cost utility (ie, number of emergency department visits saved; quality-adjusted life years) will be assessed via PROM including QoL measure. Outcomes related to the Triple Aim goal of improved patient experience of care are improved QoL for heart failure patients and improved experience of care (eg, continuity of care, comfort) as measured by the PREM tool. Other population health-related outcomes include reduction in mortality as measured by hospital data and reduction in morbidity as tracked through patient sensor data and self-report.

Primary and secondary outcomes will be identical to the feasibility study. The primary outcome will be whether or not a patient returns to an emergency department, is hospitalized, or dies within 90 days following discharge (60 days of which the patient will be monitored). Utilization data (eg, emergency department visits and admissions) will be assessed by accessing hospital and provincial database records as well as through patient self-reporting of utilization after the study period; the former is the primary method, and the latter will be considered in sensitivity analysis.

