### Study 3: Innovation Testing (Months 20-38)

During the trial period, a concurrent but separate test study will be conducted. This will entail the recruitment and engagement of an additional emergency department site during an 18-month period. The purposively selected site will be an emergency department in the Metro Vancouver area that is not involved in the cluster RCT (ie, Study 2). The innovation study will compare usual monitoring protocol to the same protocol with the addition of Sentrian intelligent monitoring software.

The goal of this study is to determine the value of the Sentrian innovation and demonstrate the value of this system to health professionals. Given the numbers of heart failure patients presenting in the emergency department in this setting over 18 months and the eligibility criteria, we expect approximately 135 patients would be eligible to enroll. Note that inclusion/exclusion criteria are the same as in the previous two studies. A minimum 60% consent rate yielding a sample size of approximately 80 patients is estimated with a maximum attrition rate of 15%. Patients will be randomized into one of two groups as they present to the emergency department: (1) regular monitoring or (2) monitoring plus Sentrian intelligent monitoring software. This innovation study is not about the outcome of revisits or admissions; rather the purpose is to determine how best to measure utilization and health professional experience in terms of decision support (that is, how the information provided by the Sentrian technology alters the physicians’ decision processes). Therefore the purpose is not to develop a model for clinical suggestions but rather to test the impact of Sentrian predictive model on physicians’ clinical decisions for this patient population. Because this study is not designed for a definitive comparison, no power calculation has been included. The primary outcome for this study will be health care utilization and will be measured by patient self-reporting as well as administrative data during the full 90-day follow-up (60 days monitoring, 30 days additional tracking). We will also collect health professionals’ perspectives around how this innovation impacted decision support.

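### Community costs in Study 2 rest mainly on one post-study patient questionnaire, although the same plan makes hospital and provincial records the primary source for utilization

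*Protocol article*

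**What the plan says.** All places are in the protocol article.

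- **Study 2, Cost-Effectiveness Evaluation: what is costed.** Besides admissions and emergency department visits, the list includes "community family physician and other health provider visits, drugs, and laboratory and other tests obtained outside the hospital".
- **Same section: sources.** Two are named: the hospitals' own administrative data, and "a simple resource utilization questionnaire administered to patients at the time of patient outcome data collection". This instrument has still to be developed. A societal perspective is planned, with patients' own spending included.
- **Same section: the comparison.** "administrative data regarding health services utilization (in particular, emergency department revisits/hospitalizations) for cases and controls will be compared". The resulting differences are then multiplied by average costs.
- **Study 2, Process and Outcome Measurement.** Utilization data, with emergency department visits and admissions given as examples, "will be assessed by accessing hospital and provincial database records" and also by patient self-report after the study period. Of these two, "the former is the primary method, and the latter will be considered in sensitivity analysis". Mortality is taken from hospital data.
- **Study 2, Data Collection Procedures.** Both arms have surveys before and after the study period only, as in Study 1. The later survey asks patients about family physician visits, emergency department visits and laboratory work.
- **Study 1, Procedures and Data Collection.** The later survey is given 90 days on, that is, 30 days after 60 days of monitoring.

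**The concern.** The project hypothesis includes cost-effectiveness, so the cost side supports a main conclusion. Community care is the part of cost that home telemonitoring could shift in either direction: earlier contact with a family physician may replace hospital use or add to it. The plan collects this part from patients, at a single contact after the period of interest.

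That creates two problems. First, data will be missing for reasons tied to outcome. A patient who dies within 90 days, which is itself a primary outcome event, leaves no report of community care used before death. A patient who withdraws or is too ill to respond leaves none either. Second, those who do respond must recall about three months of visits, tests and drugs. Response and recall may also differ by arm, because intervention patients receive training, equipment and technical support.

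An analysis plan can impute what is missing, but it cannot recover utilization that was never requested. The choice of source therefore belongs in the protocol and in the data request.

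**Working it through.** The plan gives no figure for the economic analysis that could be reproduced. The check is a comparison of sections, followed by arithmetic showing what can and cannot be said about size.

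**1. Source by item, as the article states it**

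| Item | Cost-Effectiveness Evaluation | Process and Outcome Measurement |
|---|---|---|
| Emergency visits, admissions | Administrative data | Hospital and provincial records first, self-report for sensitivity |
| Family physician and other provider visits | Hospital databases or questionnaire | Not named; falls under the general utilization rule if the examples are only examples |
| Drugs; tests outside hospital | Hospital databases or questionnaire | As above |
| Patients' own spending | Captured; source not named separately | Not mentioned |
| Deaths | Not stated | Hospital data |

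For rows two and three, a hospital database is not a natural source, since the tests are by definition obtained outside hospital and the physician visits are described as community visits. The questionnaire is what remains. Provincial records are named in one section and absent from the other.

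**2. How many reports could be missing**

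The article states no response or attrition rate for Study 2. For Study 3 it gives a "sample size of approximately 80 patients is estimated with a maximum attrition rate of 15"%, and Study 1 has the same ceiling. With assumed non-response among the 900 planned patients:

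- 5%: 0.05 × 900 = 45 missing, 855 returned
- 15%: 0.15 × 900 = 135 missing, 765 returned
- 25%: 0.25 × 900 = 225 missing, 675 returned

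**3. Why neither size nor direction follows**

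Let m be the proportion without a questionnaire in an arm, and d the mean community cost of responders minus that of non-responders. If an arm mean were taken from responders alone, its error would be m × d. The error in the incremental cost (intervention minus control) would be

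m_I × d_I − m_C × d_C.

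- Equal m and equal d in both arms: error 0.
- Common d, m_I = 0.05, m_C = 0.15: (0.05 − 0.15) × d = −0.10 d.
- Common d, m_I = 0.15, m_C = 0.05: (0.15 − 0.05) × d = +0.10 d.

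The sign of d is also open. Non-responders may be heavier users because they are sicker, or lighter users because they died early. The documents give none of m_I, m_C, d_I or d_C. If missing values were imputed, the same four unknowns would have to be assumed; with record data they are largely observed.

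**The case against.** The strongest reply is that there is no conflict. The records-first rule names emergency visits and admissions as its examples, so it may cover only those. A questionnaire for community items would then add to the rule, and a societal perspective needs some patient-reported cost in any case. The costing comparison itself leads with administrative data, in particular revisits and hospitalizations. Part of this stands. Those costs do not depend on survey return, and a questionnaire is needed for patients' own spending. It does not explain why provincial records, already to be accessed, are left out for visits, drugs and tests that the plan says it will cost.

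A second reply is that nothing shows the provincial records hold prescriptions, physician visits or laboratory tests. That stands, and the fix is conditional on it.

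A reader might also infer that the cost-utility result will be computed only in survivors who respond, because quality-adjusted life years come from a patient-reported measure ("quality-adjusted life years) will be assessed via PROM including QoL measure"). The documents do not support this. No section defines or restricts the economic analysis set. Deaths come from hospital data, so a death can enter at zero utility from its date without a survey. Cost per life year gained is a planned output, which a survivors-only set could not provide. How deaths and missing surveys are handled is commonly left to an analysis plan, which is not shown here, so silence in a condensed article is no error.

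**Conclusion.** The point holds as one about data source. As written, the costs of community visits, drugs and out-of-hospital tests rest mainly on a single post-study self-report that some patients cannot give, while another section of the same plan puts records ahead of self-report for utilization. This is a worthwhile, inexpensive improvement; it does not invalidate the economic evaluation.

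It rests on three readings: that hospital databases do not hold most care delivered elsewhere; that the questionnaire in Study 2 falls at about day 90, as in Study 1; and that the records-first rule is meant for utilization generally, or could be extended to it.

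No size is claimed. The counts of 45 to 225 missing questionnaires are illustrations, and the 15% behind 135 of 900 is an attrition ceiling borrowed from Studies 1 and 3. It would also be tempting to say that the intervention's costs will look too high and its quality-adjusted life years too low. That would need a mortality benefit, and sicker, costlier patients among those saved; the article gives no separate death rate and no community cost by which to judge either.

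**What to change.** In Cost-Effectiveness Evaluation, bring the sources into line with Process and Outcome Measurement:

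- Take community physician and other provider visits, drugs and out-of-hospital tests from the provincial records wherever those records hold the item.
- Extract them for every enrolled patient in both arms, up to day 90 or death, whether or not a survey is returned or monitoring continues.
- Keep the questionnaire for patients' own spending and for items the records do not hold, and list those items.
- State whether the records-first rule covers all utilization or only emergency visits and admissions.

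The cost is a wider data request on record access already planned. Coverage has to be checked item by item, because the documents do not state it; anything not covered stays on self-report with the limits described. The article says the questionnaire is still to be developed and the provincial trial had not yet begun, so the change can be made before data collection.

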#### Analysis

Hospital data captured and analyzed to assess outcomes will include patient revisits and admission rates within the 90 days postdischarge from the emergency department (60 days of monitoring and 30 days of additional follow-up) and days saved. Regression analysis will be used to analyze the impacts of age, gender, ethnicity, living circumstances, and attitudes towards technology on the outcomes. Individual level administrative data for heart failure patient revisits to emergency department and admission will be reviewed. Costs per patient for equipment, set-up, connectivity, and monitoring will be calculated and included in the analysis.

Content analysis of patient and health professional interviews will be used to identify themes and resulting recommendations for quality improvement of both implementation and evaluation processes to inform Study 2.

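### Valuing utilization differences at average heart-failure costs assumes equal cost per event in both arms, and the perspective called societal covers only health-system and patient costs

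*Protocol article*

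**What the plan says.** All of this is in the Cost-Effectiveness Evaluation section for Study 2 of the Protocol article, except where stated.

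- **Scope.** The incremental cost of the monitoring platform is assessed against usual care, and the team will "further track costs related to all utilization during the 90-day postdischarge period".
- **Items.** "Utilization will include hospital admissions, emergency department visits, community family physician and other health provider visits, drugs, and laboratory and other tests", the last of these when done elsewhere than in hospital.
- **Sources.** "Utilization will be captured through hospital administrative databases and a simple resource utilization questionnaire administered to patients". The questionnaire is still to be developed.
- **Comparison.** The evaluation then narrows: "administrative data regarding health services utilization (in particular, emergency department revisits/hospitalizations) for cases and controls will be compared".
- **Valuation.** The gap between the arms is turned into money as follows: "utilization rates will then be used to determine differences in cost for both patient groups based on average costs for heart failure patients".
- **Perspective.** "A societal perspective will be taken in the analysis as both government and patient out-of-pocket costs will be captured".
- **Uncertainty.** A probabilistic sensitivity analysis will vary key parameters.

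The Analysis section of Study 1 lists, among the hospital data to be assessed, revisits and admissions over 90 days ("60 days of monitoring and 30 days of additional follow-up) and days saved").

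**The concern.** There are two separate issues.

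**Costing rule.** Multiplying a difference in event rates by an average cost gives the right cost difference only if the average event costs the same in each arm. The intervention gives reason to doubt that. It is meant to detect deterioration early and start management at home, and monitoring clinicians may consult an emergency physician about a return to the ED. Either could change how ill patients are when they come back and how long they stay. Study 1 looks at days saved as well as events, so the team itself expects that savings may not lie in counts alone.

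**Perspective.** The word societal tells a reader that costs outside the health budget are included. The only reason given is that government and out-of-pocket costs are captured, and every item listed is health-care use. Unpaid caregiver time and patient time are not listed, although the intervention moves daily monitoring into the homes of people aged 65 or older.

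Cost-effectiveness is part of the project hypothesis, and the results are meant to inform provincial roll-out. A misstated saving, or a perspective that readers misunderstand, would carry into that decision.

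**Working it through.** **Plan's own figures.** The cost section states no number that can be reproduced. The illustration borrows its event rates from Power and Sample Size, so I checked that calculation first. With 450 patients per arm, 30 per hospital and an intraclass correlation of 0.005, the effective number per arm is 450 / (1 + 29 × 0.005) = 450 / 1.145 = 393.0. For 12% against 6% at two-sided 0.05 this gives 83.8% power, against the stated 84%. The rates are used as the plan means them. The power itself has no bearing on this point.

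**What the costing rule implies.** Let p_C and p_T be the event rates in the control and intervention arms, c_C and c_T the true mean cost per event in each arm, and a the average cost applied.

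- Saving under the rule: a × (p_C − p_T)
- True saving: p_C × c_C − p_T × c_T

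If a = c_C, the two agree only when c_T = c_C. Using one average per service type does not change this. The same condition then applies within each type.

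**Illustration.** Assumptions, none of them from the documents: one costed event per patient with the outcome, a = c_C = 1, and c_T = r. From the plan: p_C = 0.12 and p_T = 0.06. The rule always gives 1 × (0.12 − 0.06) = 0.060 per patient. The true saving is 0.12 − 0.06r.

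| r | True saving | Rule gives | Error, 0.060 / true − 1 |
|---|---|---|---|
| 0.8 | 0.072 | 0.060 | −17% |
| 0.9 | 0.066 | 0.060 | −9% |
| 1.0 | 0.060 | 0.060 | 0% |
| 1.1 | 0.054 | 0.060 | +11% |
| 1.2 | 0.048 | 0.060 | +25% |

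The saving is understated if intervention-arm events are cheaper and overstated if they are dearer. These percentages concern only the cost of the events. Platform cost and other utilization come on top.

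**Does the planned sensitivity analysis repair it?** Not by itself. If both arms share a unit cost, varying that cost leaves the ratio c_T / c_C at 1 in every draw.

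**Perspective, side by side.** The reason given names two payers, government and patient. The item list names admissions, ED visits, family physician and other provider visits, drugs and tests. Neither contains caregiver time, patient time or any other cost outside health care.

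**The case against.** The strongest reply is that this is ordinary costing practice. The text says average costs in the plural, after a list of service types, and quantities multiplied by a unit cost per service is a standard approach. Platform cost is assessed separately, and costs of all utilization are to be tracked. Utilization could include bed-days, since days saved appear in Study 1. Details of unit costs, clustering and resampling normally sit in a fuller plan that is not shown. On the perspective, the sentence itself discloses what it covers, and the questionnaire is not yet fixed.

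Much of this stands, and it rules out some stronger readings:

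- A reader might infer that a single average cost will be applied to everything. The text does not say so.
- A reader might infer that the saving will be overstated, perhaps two-fold. That would need avoided admissions to cost half the average. The documents say nothing about which admissions are avoided, and the error could run either way.
- A reader might infer that the interval for the cost difference will reflect event counts only. No such interval is described, and the sensitivity analysis may vary unit costs.

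The core remains. The plural reading still fixes cost per event as equal across arms. The bed-days reading would capture length of stay but not severity, and Study 2 does not promise it: the cost section points to revisits and hospitalizations. The valuation sentence also fits poorly with the commitment to track the costs of all utilization. These are things the article states, so the existence of a fuller plan does not answer them. Disclosing the scope does not make the label right.

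**Conclusion.** The point holds as a weakness in a stated costing rule and as a wrong label. Error in the cost result is possible, not shown. Its size and direction cannot be derived, because the documents give no unit costs and no length of stay by arm. The range of −17% to +25% rests on the assumed cost ratios of 0.8 to 1.2, one costed event per patient with the outcome, an average equal to the control-arm cost per event, and the planned rates of 12% and 6%. If cost per event is equal across arms and the average matches it, the rule is exact. The perspective described is health system plus patient. Cost is a secondary outcome, so the primary clinical analysis is unaffected, but the change is worth making because cost-effectiveness is part of the project hypothesis.

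**What to change.** 1. In the main cost analysis, cost each patient's ED visits and admissions from the hospital administrative record, as length of stay or case weight multiplied by a unit cost.
2. Compare mean cost per patient between arms with a method that respects hospital clustering, such as a mixed model or a bootstrap that resamples whole hospitals.
3. Keep average costing as a sensitivity analysis. The gap between the two results then shows how much the equal-cost assumption matters.
4. Relabel the perspective as health system plus patient, or add caregiver and patient time items to the resource questionnaire while it is being developed.

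The cost is a little more data extraction and analysis. Hospital administrative databases are already a planned source, but the article does not say that stay or case weight will be extracted in Study 2. The interval for the cost difference will probably be wider, because variation in cost between patients enters it. Relabelling needs only a change of wording. Added time items would lengthen the questionnaire slightly.
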